## Abstract

**Background:**

Occupational Therapists use craft-making activities as therapeutic interventions to improve physical and psychological functioning of injured people. Despite the therapeutic effects, craft-making is not routinely used in hand rehabilitation as an intervention for patients with upper limb fractures. These patients often experience physical and psychosocial issues; however, without supportive evidence, therapists hesitate to integrate craft-making into upper limb rehabilitation.

**Purpose:**

This study aims to determine the effect of a conventional therapy combined with therapeutic craft-making on disability, post-traumatic stress, and physical performance in patients with lower-third forearm fractures.

**Methods:**

Priori analysis determined that 38 patients will be needed for this superiority randomized controlled trial to be conducted in a hand and upper limb rehabilitation center. Eligible participants must comprehend English, be diagnosed with lower-third forearm fracture(s) stabilized by open reduction internal fixation, and referred to therapy within 2–4 weeks of surgery. Following the CONSORT guidelines, participants will be randomly assigned to a Control (conventional therapy) group or an Intervention (conventional therapy and craft) group. Twice weekly for 6 weeks, Therapist A will provide both groups with 1-h of conventional therapy while the Intervention group will also receive 15 min of craft-making supervised by the Researcher. The primary outcome of disability will be measured with the Quick-Disabilities of Arm, Shoulder and Hand. The secondary outcome measurements include the Patient-Rated-Wrist-Evaluation; Impact of Event Scale-revised and physical performance, i.e., the Purdue Pegboard Test, AROM, and grip strength. All outcome measures will be obtained by Therapist B prior to the 1st therapy visit and after the 12th visit. Descriptive analysis will be done for the categorical and continuous data and a mixed model ANOVA for analysis of the initial and final assessment scores within and between groups.

**Results:**

This study is ongoing.

**Discussion:**

The intent of this study is to determine if therapeutic crafts have value as an intervention when used in combination with conventional therapy for patients with lower-third forearm fractures. If the value of crafts is supported, this evidence may reduce hesitancy of therapists to implement craft-making with patients referred to hand therapy after upper limb fracture.

**Conclusion:**

This study is ongoing.

**Trial registration:**

ANZCTR, ACTRN12622000150741. Retrospectively registered on 28 January 2022 https://anzctr.org.au/Trial/Registration/TrialReview.aspx?id=382676&isReview=true..

**Supplementary Information:**

The online version contains supplementary material available at 10.1186/s13063-024-08008-w.

## Introduction

### Background and rationale {6a}

Injury to the upper limb can have serious consequences on a person’s physical, psychological, social, and financial aspects of life [1–3]. Traumatic injuries of the upper limb commonly involve fractures around the wrist joint, including the lowerthird of the forearm [4–6]. These fractures are frequently stabilized by open reduction and internal fixation (ORIF) as this technique allows for early controlled mobilization and functional use of the upper limb [4, 6].

Occupational Therapists who practice hand therapy are inclined to follow a biomedical approach, which places less emphasis on the client-centered or occupation-based approach [3, 7–9]. Therapists working in medically oriented facilities as opposed to welfare or private facilities tend to implement more physical modalities, splints, soft tissue manipulation, and mobilization [2, 3, 7]. This biomedical approach requires less active patient participation, which has been observed to not directly support the patient’s psychological well-being or occupational performance [7, 10].

Since the emergence of Occupational Therapy in 1917, therapists have been using occupation (self-care, work, leisure, and daily activities) and purposeful activity as methods to rehabilitate patients [3, 10, 11]. Craft-making, classified as a purposeful activity, is commonly implemented therapeutically [11]. As the biomedical model practice developed, therapists began to incorporate physical modalities and procedures into traditional occupation-based interventions [12, 13]. In 2019, the American Occupational Therapy Association stressed the importance of purposeful activities and provided guidelines for defining and applying purposeful activities [14]. Furthermore, therapists have been encouraged to incorporate art and craft into their patient management [12].

Therapeutically, the tangible properties of craft-making are known to provide a feeling of satisfaction, hope, and pride to the maker for a long period of time [11, 15, 16], and there is evidence to support the value of craft-making implementation during short hospital stays [17]. Craft-making is well-established as a method for providing patients with the tactile and proprioceptive sensorimotor input needed to improve fine motor control [15, 18]. Besides providing motivation, craft-making is also used for its psychophysiological and emotional effects, such as reducing pain, anxiety, and depression [12, 15].

One reason that crafts may not be routinely implemented by therapist in the hospital or hand rehabilitation settings may be simply the lack of supportive evidence [11, 15, 17].

### Objectives {7}

The objective of this study is to determine the effects of therapeutic craft-making on disability, post-traumatic stress, and physical performance compared with a 6-week conventional hand therapy protocolled approach implemented for patients with lower-third forearm fractures. Our hypotheses are that patients with lower-third forearm fractures who received 6 weeks of combined conventional therapy and therapeutic craft-making in comparison to conventional therapy only will have (1) less disability as measured by the Quick-Disabilities of the Arm, Shoulder and Hand (Quick-DASH) and the Patient Rated Wrist Evaluation (PRWE); (2) less post-traumatic stress as measured by the Impact of Event Scale-Revised (IES-R); (3) better physical performance, i.e., dexterity, as measured by the Purdue Pegboard Test (PPT), and active range of motion (AROM) of the forearm, wrist, and digits as measured by a goniometer and grip strength as measured by a Jamar™ dynamometer.

### Trial design {8}

This study is a superiority randomized controlled trial (RCT). SPIRIT checklist (Supplementary Material 1) was used as a guidance in developing this study and to ensure the quality of this study. The trial will be conducted and reported in accordance with CONSORT guidelines [19]. The CONSORT flow diagram for this study is shown in Fig. 1. Participants will be randomly assigned to either the Control group or the Intervention group.

**Fig. 1 Fig1:**
[figure not shown]
CONSORT flow diagram

## Methods

### Study setting {9}

This study will be conducted at the Hand and Upper Limb Centre, Pantai Hospital Kuala Lumpur, Malaysia.

### Eligibility criteria {10}

The inclusion criteria are patients with (1) lower-third of the forearm extra-articular, partial articular, and/or complete articular individual or combined fractures of the radius, ulna or distal radioulnar, and/or radiocarpal joint, (2) fracture(s) stabilized with ORIF technique within 2–4 weeks of referral, and (3) the ability to read and communicate in English. The exclusion criteria include (1) diagnoses of rheumatoid arthritis, multiple limb or body fractures, carpal fracture/injury, or associated peripheral nerve or tendon injury, and (2) patients with a history of cognitive or psychological impairment. For this RCT, there is no age limit to participate; however, if there is a large variance in age, sub-analysis will be performed.

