## Assignment of intervention: allocation

### Sequence generation {16a}

Group allocation will be done using a random draw method requiring the participant to draw from a large envelope holding two smaller opaque-sealed envelopes each containing a different group assignment. This study will not use an allocation ratio.

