## Statistical methods

### Statistical methods for primary and secondary outcomes {20a}

All data will be analyzed using the IBM Statistical Product and Service Solutions (IBM SPSS). Descriptive analysis for categorical data such as gender, marital status, hand dominance, type of wrist fracture, and educational level will be expressed in frequency, percentage, and proportion. Descriptive statistics will be used to analyze continuous data including age, Quick-DASH score, PRWE score, IES-R score, PPT score, AROM of the forearm and wrist, TAM for the digits, and grip strength. These results will be expressed as mean, standard deviation, minimum and maximum if the data is normally distributed or as median and interquartile range. If the data is not normally distributed, sub-analysis will be conducted to determine the outlier and the outlier will be extracted from the data set if it shows significant influence. A mixed model ANOVA will be used to test the primary outcome of this study by evaluating the mean difference between and within groups of the Quick-DASH scores obtained at baseline and after the 12th therapy session. The difference in the initial and final PRWE score, IES-R score, PPT score, AROM of the forearm and wrist, and TAM of the digits and grip strength will be analyzed using a mixed model ANOVA. Depending on the results of the aforementioned analyses, other sub-analysis will be performed as necessary.

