### Methods for additional analyses (e.g., subgroup analyses) {20b}

There are no additional analyses planned for this study.

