## Study limitations

The craft-making protocol implemented in this study was designed by activity analysis for patients with the diagnosis of lower-third forearm fractures. It is unknown if the findings of this study can be generalized to other forearm, wrist, or upper limb injuries.The use of materials with different sizes and textures can potentially change the complexity of the task and consequently affect the grading of these activities. Therefore, it is unknown if the findings of this study can be generalized if different crafts or materials are used.This small sample of participants recruited from a single centre may not represent all patients that experience lower-third forearm fractures.Self-report outcome questionnaires depend on participant perception as do the outcomes achieved in usual practice. Some perceptions are beyond the control of this study just as experienced in usual practice.Knowing that surgical methods and technical expertise in fracture fixation vary as well has a person’s rate of healing, the protocols used in this study were established to provide some control over these variables.

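### Fracture type ranges from extra-articular to complete articular in 38 patients but is neither stratified nor in the primary model; one prespecified covariate would be a cheap improvement

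*Protocol article*

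**What the plan says.** All places are in the protocol article.

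- **Eligibility criteria {10}** admits "lower-third of the forearm extra-articular, partial articular, and/or complete articular individual or combined fractures of the radius, ulna or distal radioulnar, and/or radiocarpal joint". The same section requires fixation by ORIF and excludes carpal injury, multiple fractures, and nerve or tendon injury.
- **Sequence generation {16a}:** "Group allocation will be done using a random draw method", from two envelopes. No stratification is described and no allocation ratio is fixed.
- **Statistical methods {20a}** gives fracture type a descriptive role: "hand dominance, type of wrist fracture, and educational level will be expressed in frequency, percentage, and proportion". For the comparison of arms it says: "A mixed model ANOVA will be used to test the primary outcome of this study by evaluating the mean difference between and within groups". The scores are Quick-DASH at baseline and after the last session, and no covariate is named. The section closes by allowing further unspecified sub-analyses that depend on the results.
- **Additional analyses {20b}:** "There are no additional analyses planned for this study".

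**The concern.** A variable that may well be prognostic is deliberately allowed to vary, is recorded, and then plays no part in the comparison of arms. With 17 to 19 patients per arm, simple randomisation can leave the arms visibly different in fracture mix. If fracture types recover at different rates over the six weeks, two things follow. The estimate from this one sample carries the imbalance, and the fracture-related variation in change stays in the error term.

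The timing of any remedy also matters. Adjustment is not planned, yet result-dependent sub-analysis is left open. If the baseline table shows an imbalance, adjustment would then be decided with the results in view, and a reader could not tell a planned correction from a chosen one.

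**Working it through.** **1. The plan's own figure.** Inputs from Sample size {14}: f = 0.25, two groups, m = 2 measurements, correlation 0.5, alpha 0.05, power 80%, N = 34, and 38 after 10% dropout.

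λ = N·f²·m/(1 − ρ) = 34 × 0.0625 × 2/0.5 = 8.5, on 1 and 32 df. Power is 80.7% (78.1% at N = 32). 34/0.9 = 37.8, which rounds up to 38. Both figures reproduce. The planned effect is √(4 × 8.5/34) = 1.0 SD of the change score.

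**2. Chance imbalance.** The documents do not give the share of each fracture class, so 30% and 50% are assumed. Equal arms of n are also assumed. If K of 2n patients belong to the class, the number x in one arm is hypergeometric and the gap between arms is |2x − K|/n.

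| Per arm | Class share | SD of gap | P(gap ≥ 20 points) | P(gap ≥ 30 points) |
|---|---|---|---|---|
| 17 | 30% (10 of 34) | 0.159 | 25.9% | 5.7% |
| 17 | 50% (17 of 34) | 0.174 | 16.9% | 3.8% |
| 19 | 30% (11 of 38) | 0.149 | 15.1% | 2.9% |
| 19 | 50% (19 of 38) | 0.164 | 19.4% | 5.0% |

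The probabilities do not rise smoothly with the share because the gap moves in steps of 2/n. Simulating the draw with unfixed arm sizes (N = 38) gives 18.7% and 23.5% for a gap of at least 20 points, at shares of 30% and 50%. Both lie inside the same range.

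**3. What an imbalance does to the estimate.** The group-by-time contrast is a difference in mean change, so a constant difference in level between fracture types cancels. Only a difference in change matters. The shift is the gap times the difference in change between fracture types. With that difference assumed at 5–15 Quick-DASH points:

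- gap of 20 points: 0.20 × 5 to 0.20 × 15 = 1 to 3 points
- gap of 30 points: 0.30 × 5 to 0.30 × 15 = 1.5 to 4.5 points

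The article quotes a minimal clinically important difference of 12.85.

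**4. Power with one covariate at N = 34.** If the covariate explains a share R² of the variance of change (assumed), λ becomes 8.5/(1 − R²) on 1 and 31 df. That formula takes the covariate as balanced between arms. With imbalance, λ is further multiplied by 1 − r², where r is the correlation between covariate and group. Under random allocation r² averages 1/33 = 0.03. The last column averages power over the hypergeometric distribution of step 2 and is the same to one decimal at shares of 30% and 50%.

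| R² | λ, balanced | Power, balanced | Power, averaged over imbalance |
|---|---|---|---|
| 0 | 8.50 | 80.6% | 79.4% |
| 5% | 8.95 | 82.6% | 81.3% |
| 10% | 9.44 | 84.5% | 83.4% |
| 20% | 10.63 | 88.4% | 87.4% |

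The unadjusted reference is 80.7%. The cost if fracture type is not prognostic is therefore about 0.1 point with perfect balance and 80.7 − 79.4 = 1.3 points on average. By linear interpolation the averaged figure breaks even near R² = 5% × (80.7 − 79.4)/(81.3 − 79.4) = 3.4%.

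**The case against.** The strongest reply is that this asks for an optional covariate. A group-by-time comparison without fracture type is a valid randomised analysis, and an article may leave covariates to an analysis plan that is not shown. Nothing in the article says that articular involvement predicts Quick-DASH change, and age or time since surgery could be proposed equally well. The population is narrower than the list of fractures suggests, since all patients have ORIF and complicated injuries are excluded. Baseline Quick-DASH is in the model and may already carry part of any severity effect.

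Much of this stands. It limits the point to a modest improvement whose gain may lie at the low end of the range. It does not remove the point, because the article itself states both the use of fracture type and the primary model, and leaves result-dependent sub-analysis open.

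Two stronger readings are tempting, and the documents support neither.

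- A reader might take Study limitations to say that the therapy protocols control for fracture severity, because it says "the protocols used in this study were established to provide some control over these variables". The variables named there are surgical methods, technical expertise in fixation and rate of healing. Fracture type is not among them, and the claim is only of partial control. It is true that therapy common to both arms cannot balance prognosis between them, but the sentence makes no contrary claim about fracture type. Adjusting for fracture type would not control the variables it does name, so it needs no rewrite on this account.
- A reader might call the planned analysis biased. Under sound randomisation the unadjusted contrast is unbiased on average and keeps its alpha. The issue is imbalance in one realised sample, together with lost efficiency.

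**Conclusion.** The point holds as a low-cost improvement. Fracture type is mixed by design, recorded, not stratified and absent from the stated model. A gap of at least 20 percentage points in a fracture class would occur in about 15–26% of trials and would move the estimate by 1 to 3 Quick-DASH points if fracture types differ by 5–15 points in change. Adjustment changes power at N = 34 from 80.7% to somewhere between a loss of about 1 point and a gain of 7 to 8 points over R² of 0–20%.

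Class share, prognostic strength and equal arms are assumptions, and the documents fix none of them. The sample size calculation is sound on its own terms. The benefit that does not depend on these assumptions is that the choice of adjustment would be made before the results are known.

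**What to change.** Before the data are analysed, state in Statistical methods {20a} that the primary Quick-DASH model and the secondary models include one binary covariate: any articular involvement versus extra-articular, coded from the recorded fracture type. It must enter so that it acts on the change, that is, as a fracture-by-time term in the mixed ANOVA. A term for level alone would leave the group-by-time contrast untouched.

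The cost is one sentence, one degree of freedom, and 0.1 to 1.3 points of power if fracture type is not prognostic. The article does not say how fracture type is coded. Eligibility is already worded by articular involvement, so the split should be obtainable, but the sponsor should confirm this. The binary split merges partial with complete articular fractures and ignores single versus combined ones. With 34 to 38 patients, that coarseness is the price of using a single term. Trial status describes recruitment as ongoing, so on that footing the change can still be prespecified.

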### Who will obtain informed consent? {26a}

During the first therapy visit, the Researcher will brief participants regarding the study and obtain informed consent. Participants will need to read the information sheet and sign the informed consent form before participating in this study.

### Additional consent provisions for collection and use of participant data and biological specimens {26b}

Not applicable as no biological specimens will be collected as part of this study.

## Interventions

### Explanation for the choice of comparators {6b}

#### Control group

Participants in the Control group will receive 1-h of conventional therapy described in the protocol (Table 1) including hot/cold packs, ultrasound, joint mobilization, AROM exercises including tendon gliding, passive stretching, scar massage, and therapeutic exercise to improve pinch, grasp, and forearm strength. All conventional therapy sessions will be conducted by Therapist A (Fig. 1).

**Table 1 Tab1:** Conventional therapy protocol for both the Control and Intervention groups

Week	Therapy
1	Heat/cryotherapy Active mobilization of wrist and forearm Mobilization of uninvolved joints Light grasp and pinch Tendon gliding Ultrasound Scar massage
2	Heat/cryotherapy Gentle stretching of wrist and forearm Mobilization of uninvolved joints Grasp and minimally resistive activities Ultrasound Scar massage
3	Heat/cryotherapy Passive stretching to gain full range of motion of wrist and forearm Light forearm strengthening Moderate resistive grasp and pinch Ultrasound Scar massage
4	Heat therapy Passive stretching to gain full range of motion of wrist and forearm Forearm strengthening Moderate resistive grasp and pinch Ultrasound Scar massage
5	Heat therapy Passive stretching to gain full range of motion of wrist and forearm Forearm strengthening Functional activities—pinch tree and EZ board Ultrasound Scar massage
6	Heat therapy Passive stretching to gain full range of motion of wrist and forearm Forearm strengthening Functional activities—pinch tree and EZ board Ultrasound Scar massage

### Intervention description {11a}

#### Intervention group

During 1-h of conventional therapy, Therapist A will follow the protocol described in Table 1. After conventional therapy, the Researcher will provide an additional 15 min of therapeutic craft-making activities as delineated in the template for intervention description and replication (TIDieR) in Table 2. These activities will be done in a separate room and the participants will be given a 5–10-min break between conventional therapy and the therapeutic craft-making sessions. The 6 weeks of therapeutic craft-making is outlined in protocol format in Table 3. This craft-making protocol was developed through activity analysis completed by six Occupational Therapy students explicitly for this study and will be conducted according to the list of craft-making protocol developed earlier (Table 3 and Fig. 2).

**Table 2 Tab2:** Template for therapeutic craft-making intervention description and replication (TIDieR) checklist (Supplementary Material 2)

	Therapeutic craft-making
Why	A method to provide sensorimotor input for improvement of fine motor skills and regulate psychophysiological and emotional response
What	All materials are available in craft shops or online marketplaces. These included air dry clay, silicone mold, papers, quilling papers, paper glue, quilling pen, batik cloth, cloth dyes, dropper, origami papers, beads, elastic thread, stamps, stamp pads, ice-cream sticks, hot glue, Perler beads, Perler board, forceps, strings, felt cloths, cottons, needles, metal ruler, soap base, perfume, and soap dye
Who provided	The Researcher
How	1 on 1 individually
Where	A designated room away from the general treatment area
When and how much	After 1-h of conventional therapy, twice weekly for 6 weeks for approximately 15 min per session
Tailoring	Craft will be adapted to individual’s hand function and performance Simplification of tasks or assistance will be provided if participant is struggling to complete the craft

**Table 3 Tab3:** Craft-making protocol for intervention group

Week	Craft	Steps
1	Air dry clay art	Open package of clay and take out a small amount of clay Knead clay with fingers Insert clay into mold Even out the clay using fingertips Remove excess clay
	Quilling	Pour a small amount of glue on unwanted paper Choose a piece of quilling paper and insert one end into the quilling pen Turn the pen to roll the paper until the end Shape quilled paper according to design Place the quilled paper on glue to apply glue Glue quilled paper on card, press until it firmly sticks
2	Batik painting	Dominant hand Dip paintbrush in fabric dye and transfer to palette Dilute dye with water Color the batik Clean paint brush by dipping it into water Non-dominant hand Open dropper’s cap Point the tip of the dropper onto the desire area on the batik Squeeze dropper Use the dropper point to spread the color around
	Origami	Take a piece of origami paper Flip and fold paper according to the steps Use fingertip to press on folded sides
3	Threading beads	Cut elastic thread and tie a knot on one end of the thread Take beads from packet/container Treading beads into the other end of the thread Tie both ends together once finished Cut excess thread
	Card making	Cut A4 paper into half and trim edges Fold the paper in half and cut out the design Pick up alphabet stamps Stamp on ink pad then stamp on the card to finish sentences Glue the A4 paper to card paper with quilling
4	Cloth stamping	Fold newspaper in half and insert it into inner layer of the shirt Pick up a stamp and apply fabric dye using paintbrush Put paintbrush into a cup of water Turn over the stamp and put on the cloth Press on stamp for 5 s Carefully remove stamp
	Wooden frame design	Apply hot glue to the end of stick Glue wooden sticks in parallel to make a square frame Apply instant glue on decorative clay Glue decorative clay on to the frame
5	Sewing	Insert thread into the hole of a needle Tie a knot at the end of the thread Match the layer of design and sew the edge of the design until ¾ complete Put cotton into the opening Sew the product until finish Tie a few knots and trim the excess thread
	Perler beading	Pick a design and take a Perler board Use a finger tweezer to pick up Perler beads Place beads on board according to design Carefully place the iron paper against the completed beaddesign Iron Perler beads until it sticks together Flip the beads to the other side and continue to iron Remove Perler from iron paper
6	Braiding and cup mat	Find the midpoint of a rope and tie a knot at the middle of another rope Start braiding from top Tape to secure the top of the rope on table Continue braiding until finish Use hot glue to secure the finished end Curl the rope, glue, and then roll the braided rope into a circular shape
	Soap	Cut the soap base into small pieces using a metal ruler Put soap pieces into a metal cup Heat the metal cup in hot water Put a drop of soap dye and fragrance into melting soap Stir soap slowly using a stick Pour mixture into the mold Spray alcohol on the soap to reduce bubbles

The copyright of this craft-making protocol for lower-third forearm fracture is owned by Universiti Kebangsaan Malaysia

